**LIST OF ABBREVIATIONS AND RELEVANT DEFINITIONS**

|       |                                                                                                              |
|-------|--------------------------------------------------------------------------------------------------------------|
| BMI   | Body mass index                                                                                              |
| CCMO  | Central Committee on Research Involving Human Subjects (in Dutch: Centrale Commissie Mensgebonden Onderzoek) |
| CV    | Curriculum Vitae                                                                                             |
| DIT   | Diet induced thermogenesis                                                                                   |
| EE    | Energy expenditure                                                                                           |
| EGCG  | Epigallocatechin gallate                                                                                     |
| FA    | Fatty acids                                                                                                  |
| FFM   | Fat free mass                                                                                                |
| FM    | Fat mass                                                                                                     |
| FMI   | Fat mass index                                                                                               |
| IC    | Informed Consent                                                                                             |
| IMP   | Investigational Medicinal Product                                                                            |
| METC  | Medical Research Ethics Committee (MREC) (in Dutch: Medisch Ethische Toetsing Commissie)                     |
| PAL   | Physical activity                                                                                            |
| REE   | Resting energy expenditure                                                                                   |
| RQ    | Respiratory quotient                                                                                         |
| (S)AE | (Serious) Adverse Event                                                                                      |
| SEM   | Standard error of the mean                                                                                   |
| SPSS  | Statistical Package for the Social Sciences                                                                  |

|      |                                                                                                             |
|------|-------------------------------------------------------------------------------------------------------------|
| TBW  | Total body water                                                                                            |
| TFEQ | Three Factor Eating Questionnaire (TFEQ)                                                                    |
| WHR  | Waist-to-hip ratio                                                                                          |
| Wbp  | Personal Data Protection Act (in Dutch: Wet bescherming persoonsgegevens)                                   |
| WMO  | Medical Research Involving Human Subjects Act (in Dutch: Wet Medisch-wetenschappelijk Onderzoek met Mensen) |

## SUMMARY

**Rationale:** Green tea might have positive effects for weight control and body composition via several approaches such as a positive effect on the gut flora, a decrease in fat absorption from the intestines and an increase in resting energy expenditure.

**Objective:** To investigate the long-term effects of green tea on gut flora, fat absorption, resting energy expenditure and body composition.

**Study design:** The study will be conducted in a randomized, placebo-controlled, double-blind parallel design with four groups consisting of control groups and green tea groups with normal weight subjects and obese subjects. At three time points (baseline, 6 weeks and 12 weeks) faeces are collected for analyzing the gut flora and fat absorption. Furthermore, measurements of resting energy expenditure and body composition will be conducted. Activity will be measured throughout 3 weeks.

**Study population:** a hundred healthy subjects (50 males and 50 females) with a body mass index (BMI) between 18.5-25 kg/m^2 and ≥30 kg/m^2 and aged between 18-50 years will be included in the study. All subjects will be non-smoking, weight stable, dietary unrestrained, not drinking tea and at most moderate alcohol and caffeine consumers. Subjects will be free of medication except for oral contraceptives use in women.

**Intervention:** Subjects will receive either green tea or placebo in capsule form after their baseline measurement, which they have to consume daily for a period of twelve weeks.

**Main study parameters/endpoints:** Gut flora composition, fat absorption, body composition and resting energy expenditure.

**Nature and extent of the burden and risks associated with participation:**

The study does not include any major risk for the subjects. The collection of faeces will be harmless. Anthropometric and body composition measurements will not be invasive for the subjects. Deuterium dilution has been shown to be a safe method for determining total body water. Furthermore, the registration of oxygen consumption and carbon dioxide production with the ventilated hood will be performed. The air in the hood is continuously regulated.

Administering green tea will not form any health risk. Green tea is a natural product.

**Benefit:** This study does not have any benefits for the subjects themselves, but will give possible new knowledge for the treatment of obesity.

## 1. INTRODUCTION AND RATIONALE

Obesity is a result of an energy imbalance that develops when energy intake exceeds energy expenditure. It is associated with an increased risk on developing Type 2 Diabetes, cardiovascular diseases and several cancers (1). Obesity has also been shown to be associated with an increased risk of mortality; overweight and obesity are the fifth leading risk for global deaths (2).

Tea is a widely consumed beverage. Green tea is made from the fresh leaves of *Camellia sinensis* L. and contains polyphenols. The main green tea polyphenols are catechins. The health beneficial effects of green tea have been attributed mainly to these catechins. The most abundant catechin is epigallocatechin gallate (EGCG).

Green tea might have positive effects for weight control and body composition via several approaches such as a positive effect on the gut flora, a decrease in fat absorption from the intestines and an increase in resting energy expenditure.

Green tea appeared to increase the 24-h energy expenditure (EE) and fat oxidation in humans (3). Thereby green tea can induce weight loss and is thought to be useful as an antiobesity compound.

Furthermore, green tea polyphenols might also interfere with fat absorption in the intestine, resulting in decreases in the digestible energy of the diet. A decrease in fat absorption, inferred from increases in faecal fat excretion has been observed in several animal studies (4-6). Raederstorff et al investigated the effect of green tea catechins on lipid metabolism in rats. They showed that EGCG decreased plasma total cholesterol and non-HDL cholesterol concentrations and increased faecal excretion of total lipids and cholesterol (6).

Another animal study also investigated the effect of (EGCG) on obesity and energy metabolism in mice. EGCG attenuated diet-induced body fat accretion in mice and apparently promoted fat oxidation (4).

EGCG has been reported to inhibit the intestinal absorption of lipids and it is suggested that one of the underlying mechanisms by which EGCG affects lipid metabolism is by interfering with the micellar solubilisation of cholesterol in the digestive tract, which then in turn decreased cholesterol absorption (5, 6).

It is also suggested that green tea polyphenols have a positive effect on the gut flora. Trillions of bacteria (microbiota) live in the human gastrointestinal tracts and they all have their own genome. Recent evidence suggests that the trillions of bacteria that normally reside within the human gi-tract affect nutrient acquisition and energy regulation (7). Two groups of beneficial bacteria are dominant in the human gut, the *Bacteroidetes* and the *Firmicutes*. The relative proportion of *Bacteroidetes* to *firmicutes* is decreased in obese people compared to lean people. Obese and lean people have different gut microbiota. This finding raise the posibility that the gut microbiota has an important role in regulating weight (8)

Green tea is rich in polyphenols. A supplementation with polyphenols with high bioavailability in obese individuals, with higher *Firmicutes/Bacteroidetes* community ratio phenotype, when associated to a probiotic restricted diet, is proposed for weight loss (9).

Green tea might have a positive effect on the gut flora, a decrease in fat absorption from the intestines, an increase in resting energy expenditure and a decrease in the *Firmicutes/Bacteroidetes* ratio. Several animal studies investigated the effect of green tea consumption on fat absorption however it is necessary to investigate whether green tea also lowers the fat absorption and increases the fat excretion in humans. Therefore we hypothesize that green tea consumption has positive effects for weight control via a decrease in fat absorption, an increase in fat excretion and a decrease in the *Firmicutes/Bacteroidetes* ratio.

## 2. OBJECTIVES

The objective of this study is to investigate the long-term effects of green tea on gut flora, fat absorption, resting energy expenditure and body composition. The primary aim of the present study is to examine whether green tea supplements affect fat metabolism, gut flora and body weight.

This primary objective implies that green tea increases faecal fat and decreases fat absorption, resulting in decrease in digestible energy of the diet. Green tea may inhibit lipase activity. Inhibition of digestive lipase activity could significantly affect dietary lipid absorption and could increase lipid excretion into the faeces. Faecal fat excretion will be measured to determine the lipid absorption (10).

Previous studies have shown comparable effects in animal studies (4-6). This study needs to determine whether green tea also increases faecal fat and lowers the fat absorption in humans and will test the hypothesis that the increase in faecal fat will be larger in the green tea conditions compared to the conditions without green tea.

Furthermore we will investigate whether green tea has positive effects on gut flora and will increase the relative proportion of *Bacteroidetes* to *Firmicutes* and that this change in *Firmicutes/Bacteroidetes* ratio will be larger in obese subjects compared to normal weight subjects. Metabolism of polyphenols by microbiota involves the cleavage of glycosidic linkages. Glycans, which are the product of glycosidic cleavage, are necessary for survival of the intestinal microbiota as a nutrient foundation. *Firmicutes* possess a disproportionately smaller number of glycan-degrading enzymes than *Bacteroidetes*. Furthermore, *Firmicutes* are more repressed than the *Bacteroidetes* by phenolic compounds' antimicrobial properties. The *Bacteroidetes* community prevails following dietary polyphenol intake and its fermentation to phenolic compounds, due to having more glycan-degrading enzymes, so this may thus be a mechanism by which dietary polyphenols exert their weight lowering effect (9).

Finally, we will investigate whether a supplementation with green tea polyphenols is proposed for weight loss via an increase in the resting energy expenditure and fat oxidation.

Four groups consisting of control groups and green tea groups with normal weight subjects and obese subjects will be applied in order to completely answer the research questions:

- Normal weight without green tea (NW/control)
- Obese without green tea (Ob/control)
- Normal weight with green tea (NW/GT)
- Obese with green tea (Ob/GT)

### 3. STUDY DESIGN

#### 3.1. Study design

The study will be conducted in randomized, placebo-controlled, double-blind parallel design with four randomly sequenced experimental conditions.

#### 3.2. Intervention

Subjects will visit the university three times (baseline, 6 weeks and 12 weeks) and three days before each visit faeces will be collected for analysing the gut flora and fat absorption. They will be asked to travel by public transport or car, in order to avoid physical activity that would increase resting energy expenditure (REE). Subjects will arrive in fasted state at 08:30 h. They will empty their bladder before the test. After resting on a bed for 30 min, the REE and the substrate oxidation of the subjects will be measured for 30 min by means of an open-circuit, ventilated hood system. Subjects will receive either green tea or placebo in capsule form after their baseline measurement, which they have to consume daily for a period of twelve weeks.

All faeces will be collected in pre-weighed plastic containers on the last day before each visit period. Faecal fat excretion will be assessed at baseline and after 6 and 12 weeks. Body weight will also be measured at baseline and after 6 and 12 weeks.

Subjects will be asked not to change their food pattern during this period of twelve weeks. They will be instructed to abstain from tea and dairy products like milk, cheese, pudding and yoghurt and to use less than 100 ml caffeine-containing beverages per day like coffee, cola-type soft drinks and energy drinks.

The subjects will be instructed to maintain their habitual activity level. Physical activity will be determined with the use of a triaxial accelerometer for movement registration (Tracmor; Philips, Eindhoven, Netherlands) during three weeks (baseline, week 6 and week 12).

#### 3.3. Flow chart

|                     | Baseline | 6 weeks | 12 weeks |
|---------------------|-----------------|----------------|-----------------|
| Body weight         | x               | x              | x               |
| Fat mass (BodPod0 x |                 | x              | x               |
| Collecting faeces   | x               | x              | x               |
| REE                 | x               | x              | x               |
| Physical activity   | xxx             | xxx            | xxx             |
| TBW (Deuterium)     | x               |                | x               |
| WHR                 | x               |                | x               |

## 4. STUDY POPULATION

### 4.1. Population

Subjects from the student population will be recruited by advertisements on notice boards at Maastricht University and in local newspapers. Healthy, non-smoking, males and females who are normal weight (Body Mass Index (BMI) 18.5-25 kg/m^2) or obese (BMI ≥30 kg/m^2) and aged between 18-50 yrs will be recruited for an initial screening, whereafter a total of 100 subjects (50 males and 50 females) will be included in the study. During the screening, subjects will undergo anthropometric and body composition measurements, and will complete questionnaires related to health, smoking behaviour, use of medication, alcohol consumption, probiotic consumption, physical activity, eating behaviour, mood and anxiety.

|              | Age 18-35 years |          | Age 35-50 years |          | Total |
|--------------|-----------------|----------|-----------------|----------|--------------|
|              | BMI 18.5-25     | BMI > 30 | BMI 18.5-25     | BMI > 30 |              |
| Male         | 12              | 12       | 12              | 12       | 48           |
| Female       | 12              | 12       | 12              | 12       | 48           |
| Total | 24              | 24       | 24              | 24       | 96    |

### 4.2. Inclusion criteria

A total of 100 subjects (50 males and 50 females) with a BMI between 18.5-25 kg/m^2 and ≥30 kg/m^2 and aged between 18-50 years will be included in the study. All subjects will be non-smoking, healthy, weight stable, dietary unrestrained, not using a more than moderate amount of alcohol (<10 consumptions/wk) or more than 100 mg caffeine per day, not drinking tea, not using probiotics, being weight stable (weight change < 3kg during the last 6 months), dietary unrestrained and not using antibiotics during the last 6 months. The Dutch translation of the Three Factor Eating Questionnaire (TFEQ) will be used to determine eating behaviour (11). Non-restrained eaters (<9 times factor 1), these are persons who are not consciously occupied with food and who are caloric restricted, will be selected. Subjects will be free of medication except for oral contraceptives use in women.

### 4.3. Exclusion criteria

Subjects will be excluded if they are not healthy, smoking, using a more than moderate amount of alcohol (>10 consumptions/wk), using more than 100 mg caffeine per day, drinking tea, using probiotics, not being weight stable, dietary restraint, using medication or supplements except for oral contraceptives in women, using antibiotics or if they do not meet the criteria for BMI and age. Pregnant and lactating women, and subjects with allergies for the used food items will also be excluded from participation.

#### 4.4. Sample size calculation

The primary endpoint of this study is the change in gut flora and fat absorption.

For the sample size calculation the following formula was used:

$$N = 2 + (Z_{1-\beta} + Z_{1-\alpha/2})^2 \times \sigma^2 / (\mu_{GT} - \mu_{CONTROL})^2$$

Subject population size was calculated using G\*Power 3.1.2 where  $\alpha$  was 0.05,  $\beta$  was 0.95 using group mean body weight changes from past papers (12) to calculate the effect size, the population was finalized as 45 per group and an additional 5 (drop-out of 10%) will be included in the population size for any unforeseeable circumstances which may lead to subjects dropping out.

The calculated sample size will be:

|                    |           |           |
|--------------------|-----------|-----------|
| Means:             | u1 = 72.5 | u2 = 71.4 |
| Standard deviation | SD1= 1.4  | SD2= 1.7  |

Confidence interval is  $\alpha=0.05$ , for  $\beta=0.95$

$$N1 = N2 = 2 + (Z(1-\beta) + Z(1-\alpha/2))^2 \times \frac{(\sigma_1^2 + \sigma_2^2)}{(\mu_1 - \mu_2)^2}$$

45 people per condition (two conditions; green tea and placebo).

Taking a drop-out of 10% into account, 50 subjects will be included per condition and herewith 100 subjects will be included in the experiment.

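### The 45 subjects per condition in section 4.4 do not follow from its own two-sided formula and inputs: 95% power needs 54, and 45 give about 91%

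*Protocol*

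**What the plan says.** Protocol section 4.4 gives a formula, its inputs and a result.

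- **Error rates.** Alpha is 0.05, and beta is twice given as 0.95. The first formula contains "Z_{1-\beta} + Z_{1-\alpha/2})^2", and the second has the same two normal quantiles. Both are therefore two-sided.
- **Inputs.** The means are "u1 = 72.5 | u2 = 71.4", and the SDs are 1.4 and 1.7. The text describes their source, and the number reached, as "using group mean body weight changes from past papers (12) to calculate the effect size, the population was finalized as 45 per group".
- **Formulas.** The first multiplies the squared sum of quantiles by a single σ². The second multiplies it by σ₁² + σ₂². Both add 2 and divide by the squared difference in means.
- **Result.** "45 people per condition (two conditions; green tea and placebo"; then "Taking a drop-out of 10% into account, 50 subjects will be included per condition", 100 in all.

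Section 4.1 says that "a total of 100 subjects (50 males and 50 females) will be included in the study", and 4.2 repeats the 100. The recruitment table in 4.1 has eight cells of 12 (sex by age band by BMI band) and totals 96. Section 6.5 says that withdrawn subjects are replaced. Section 8.2 plans ANOVA at p < .05 and mentions no one-sided test.

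**The concern.** All the ingredients of the calculation are printed, so a reader can check it, and the result does not come out. Change in body weight is one of the primary endpoints in section 6.1.1, and this is the only power statement in the protocol. If the trial shows no weight difference, a reader will take it that an effect of 1.1 kg would have been detected with 95% power. On the protocol's own inputs that is not so.

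The surrounding defects make the figure harder to repair by guesswork: a mislabelled error rate, two formulas that are not equivalent, means that do not fit their description, and two different recruitment totals.

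**Working it through.** **Inputs, all from section 4.4.** Difference 72.5 − 71.4 = 1.1. Variances 1.4² = 1.96 and 1.7² = 2.89, sum 4.85. Pooled SD √(4.85/2) = 1.557, so the standardised difference is 1.1/1.557 = 0.706. Quantiles: z(0.975) = 1.960, z(0.95) = 1.645.

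**1. The printed second formula, with 0.95 read as power.**
2 + (1.645 + 1.960)² × 4.85/1.21 = 54.1 per condition. The protocol states 45, so its figure is not reproduced.

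**2. Exact two-sided t test** (noncentral t, pooled SD 1.557). Power is 94.98% with 53 per condition and 95.3% with 54. The smallest adequate number is 54.

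**3. Power of the stated numbers, two-sided 0.05.**

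| Evaluable per condition | Power (t test) |
|---|---|
| 45 | 91.2% |
| 50 (nobody lost) | 93.8% |
| 54 | 95.3% |

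The drop-out step is correct in itself: 45/0.9 = 50.

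**4. Where 45 might come from.** Several slips lead to it or near it:
- one-sided alpha 0.05, 95% power, exact t test: 45 (power 95.4%); the printed formula with one-sided alpha gives 45.4;
- the printed two-sided formula at 90% power: 2 + (1.282 + 1.960)² × 4.85/1.21 = 44.1, rounded up to 45;
- the printed two-sided formula at 95% power with SD 1.4 in both groups: 2 + (1.645 + 1.960)² × 3.92/1.21 = 44.1, rounded up to 45.

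None of these is the calculation that 4.4 describes.

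**5. The two formulas.** They differ by σ² against σ₁² + σ₂². If σ² is taken as the pooled variance 2.425 (an assumption, since 4.4 does not define it), the first formula gives 2 + (1.645 + 1.960)² × 2.425/1.21 = 28.0, about half the second.

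**6. The beta label.** Taken literally, beta = 0.95 makes z(1−β) = −1.645, and the second formula gives 2.4 per group. Nobody intends that. The label is wrong, and power is meant.

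**7. The inputs.** Values of 72.5 and 71.4 are body weights, not weight changes. The SD that the calculation needs is that of the 12-week change, and 4.4 does not say whether 1.4 and 1.7 are that.

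**8. The totals.** The table gives 8 × 12 = 96, against 100 in the text. If 96 are split 1:1 (an assumption, since the table does not show treatment), there are 48 per condition. With every withdrawal replaced, power is 92.9%. With 10% unreplaced drop-out, 96 × 0.9/2 = 43.2 per condition, and power is about 90%.

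**The case against.** The strongest reply is that the error is small on the protocol's own inputs. About 91% against 95% is still ample power, and 93.8% is reached if all 50 per condition complete or withdrawals are replaced as 6.5 provides. That stands, and it limits the size of the point. It does not make 45 the answer to the calculation as printed, and even 50 completers fall short of the stated 95%.

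Three stronger readings are tempting and should be resisted.

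- **That the trial was sized one-sided.** A one-sided exact t test does return 45, which may explain the figure. But other slips also round up to 45, both formulas carry α/2, and no section states a one-sided test. It is an inference about the cause only.
- **That the table cuts power to 90%.** This needs a 1:1 split of 96 and unreplaced drop-out, while 6.5 plans replacement. The Summary, 4.1, 4.2 and 4.4 all say 100, so the table is the outlier. The contradiction is certain; the loss of power is not.
- **That the SDs are impossible or are really standard errors.** They are labelled as standard deviations, and nothing in the protocol suggests otherwise. Values of 1.4 to 1.7 kg would be odd for absolute weight across normal-weight and obese subjects, but the text speaks of changes, and nothing in the document contradicts them as SDs of change. What can fairly be said is that the means are shown on one scale and described on another.

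**Conclusion.** The point holds. With two-sided alpha 0.05, 95% power, a difference of 1.1 kg and SDs 1.4 and 1.7, section 4.4 should arrive at 54 evaluable per condition, not 45. The stated 45 give about 91% power. This rests only on the printed inputs and on reading 0.95 as power, the one reading that makes sense; it does not depend on how 45 arose.

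The beta label, the two unequal formulas, the mismatch between means and their description, and 96 against 100 are established from the text. The power attached to 96 subjects, about 90% to 93%, is conditional on a 1:1 split and on whether withdrawals are replaced.

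The protocol does not show that power is far below 91%. That would need a larger SD of change than the one printed, and the document gives no such figure.

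**What to change.** Amend sections 4.1 and 4.4:

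1. Replace both statements of beta as 0.95 by the power, and keep only the second formula (with σ₁² + σ₂²).
2. State that 45 evaluable subjects per condition give about 91% power at two-sided 0.05 for a difference of 1.1 kg with SDs 1.4 and 1.7, and that 54 would be needed for 95%.
3. Present the inputs as the difference in, and the SD of, the 12-week weight change. Optionally add power over a range of SDs labelled as assumed. For 45 per condition and 1.1 kg, SDs of 2.0, 2.5 and 3.0 give 73%, 54% and 41%.
4. Make the table in 4.1 and the text give the same total, and state the power for it. If 96 is kept and split 1:1, that is about 93% with withdrawals replaced and about 90% with 10% unreplaced drop-out.

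The cost is a wording amendment and a less favourable power statement. No extra subjects are required. Holding to 95% instead would mean 54 evaluable, or 54/0.9 = 60 enrolled, per condition (120 in all).
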